## Abstract

**Background:**

Palliative care is an effective model of care focused on maximizing quality of life and relieving the suffering of people with serious illnesses, including dementia. Evidence shows that many people receiving care in nursing homes are eligible for and would benefit from palliative care services. Yet, palliative care is not consistently available in nursing home settings. There is a need to test pragmatic strategies to implement palliative care programs in nursing homes.

**Methods/design:**

The UPLIFT-AD (Utilizing Palliative Leaders in Facilities to Transform care for people with Alzheimer’s Disease) study is a pragmatic stepped wedge trial in 16 nursing homes in Maryland and Indiana, testing the effectiveness of the intervention while assessing its implementation. The proposed intervention is a palliative care program, including 1) training at least two facility staff as Palliative Care Leads, 2) training for all staff in general principles of palliative care, 3) structured screening for palliative care needs, and 4) on-site specialty palliative care consultations for a one-year intervention period. All residents with at least moderate cognitive impairment, present in the facility for at least 30 days, and not on hospice at baseline are considered eligible. Opt-out consent is obtained from legal decision-makers. Outcome assessments measuring symptoms and quality of care are obtained from staff and family proxy respondents at four time points: pre-implementation (baseline), six months after implementation, at 12 months (conclusion of implementation), and six months after the end of implementation. Palliative care attitudes and practices are assessed through surveys of frontline nursing home staff both pre- and post-implementation. Qualitative and quantitative implementation data, including fidelity assessments and interviews with Palliative Care Leads, are also collected. The study will follow the Declaration of Helsinki.

**Discussion:**

This trial assesses the implementation and effectiveness of a robust palliative care intervention for residents with moderate-to-advanced cognitive impairment in 16 diverse nursing homes. The intervention represents an innovative, pragmatic approach that includes both internal capacity-building of frontline nursing home staff, and support from external palliative care specialty consultants.

**Trial registration:**

The project is registered on ClinicalTrials.gov: NCT04520698.

**Supplementary Information:**

The online version contains supplementary material available at 10.1186/s12904-023-01226-0.

## Background

Nursing homes (NH) are an important site of care for people with dementia, particularly near the end of life. A substantial majority of NH residents (72%) have cognitive impairment, and half have a formal diagnosis of dementia [1, 2]. By 2030, an estimated 40% of all U.S. deaths among older Americans will occur in NHs, and 70% of people with advanced dementia will live their final days in a NH [3]. Unfortunately, NH care is associated with inadequate symptom control, low family satisfaction, burdensome treatments, and poor quality of care at the end of life [4–6]. Palliative care (PC) is an effective patient- and family-centered model of care focused on maximizing quality of life and relieving the suffering of people with serious illnesses. Studies have indicated that PC can improve NH resident outcomes, demonstrating better pain management, lower re-hospitalization, greater family satisfaction, and higher likelihood of receiving treatments consistent with one’s goals of care [7–11]. Experts have called for PC to be integrated as a standard model of care for all long-stay NH residents, but only isolated examples of successful implementation exist [12–15]. Despite evidence that PC could enhance NH care, PC remains highly underutilized, particularly among residents with dementia [8, 16–21]. In this manuscript, we describe a clinical trial to test the implementation and effectiveness of one such intervention.

## Project overview

This clinical trial is an evidence-informed intervention that provides internal capacity-building strategies for increasing PC knowledge and practice in NHs, as well as external specialty PC support to enhance the overall quality of care and quality of life for residents with dementia*.* The UPLIFT-AD (Utilizing Palliative Leaders in Facilities to Transform care for people with Alzheimer’s Disease) intervention includes training in-house PC Leads on key topics in PC and the Lead role, facility-wide PC overview education for staff, a structured process for screening for PC needs, and external specialty PC clinicians providing consultations in the facility. This federally funded clinical trial (NCT04520698) tests the effectiveness of the intervention, while assessing the implementation context [22]. The trial will include 16 NHs distributed evenly between Indiana and Maryland, with a target enrollment of 640 residents with moderate-to-advanced cognitive impairment. Enrollment of residents began in September 2021 and the first two facilities entered the implementation phase in January 2022. Final data collection for all facilities is expected to conclude in early 2025.

Collected via structured surveys, trial outcomes include changes in 1) resident symptoms and 2) perceptions of quality of care. Given the cognitive limitations of the study population, outcome data are collected from proxy respondents: NH staff and family/surrogate decision-makers for each resident. Secondary outcomes include NH staff knowledge and attitudes toward palliative care, collected at baseline and six months post-implementation.

After recruitment of a NH, there is a pre-implementation period of up to six months, during which participants are enrolled, PC Leads are identified and trained, and baseline data are collected. The one-year intervention period begins when the first on-site visit from the external specialty PC consultant occurs. Follow-up data collection occurs six months after implementation and at the conclusion of implementation. The fourth and final data collection time point occurs six months following the end of the implementation period. Figure 1 shows the timeline for each NH, including data collection time points.

**Fig. 1 Fig1:**
[figure not shown]
Timeline of activities in each nursing home

## Methods and design

### Study design and setting

UPLIFT-AD is a pragmatic trial with a modified stepped wedge design, where the intervention is rolled out in four waves. Each wave includes four facilities (two each in Indiana and Maryland). The sequence of the intervention rollout at the participating sites, however, is not fully randomized as in the traditional stepped wedge design to accommodate the logistics of rollout at specific NHs. Such ad-hoc modifications have been used in previous NH-based pragmatic trials [23]. In Indiana, the first four facilities were recruited and randomized to Waves 1 and 2. Further randomization of facilities, however, has proven too challenging, due to the many factors influencing successful NH recruitment. After discussion with the project Data Safety and Monitoring Board, the design was modified from a randomized to a non-randomized stepped wedge trial.

Eligible NHs must be within a 40-mile radius of the respective PC consultant practice in Indiana and Maryland (there are > 100 NHs in that radius for each state). NHs must be Medicare and Medicaid-certified and have a significant long-stay census, with a goal of having 40 residents who would meet inclusion criteria for the trial. NHs are excluded if they already have external PC consultants who make routine resident visits in the facility or if the facility has an active internal PC program.

### Objectives

The study will 1) evaluate the effectiveness of the UPLIFT-AD implementation by comparing surrogate-reported symptom management and quality of care of residents with dementia in intervention and control periods using structured outcome assessments; 2) evaluate the implementation of UPLIFT-AD using the RE-AIM (Reach, Effectiveness, Adoption, Implementation, and Maintenance) framework; and 3) compare staff knowledge and attitudes about PC, using a validated survey tool.

### Recruitment of nursing homes

Eligible facilities are contacted for additional information, including assessing whether organizational priorities are in alignment with PC services and the degree of interest in the study of key leaders. The research team and PC consultation partners conduct outreach to corporate contacts as well as facility-level leadership, including the facility administrator, director of nursing, and medical director, during the recruitment process. The facility administration signs a Research Collaboration Agreement prior to their involvement in the trial.

Participating NHs receive financial support ($15,000) to offset costs for their participation/partnership in the project (including staff time for data collection and trainings) and to facilitate the initial development of a sustainable PC program. To receive the financial stipend, project milestones must be met. The initial stipend of $10,000 is invoiced following signed agreements, initial in-facility kick-off meeting, and identification of PC Leads. The final $5,000 is invoiced following final data collection.

### Research ethics

The UPLIFT-AD protocol is approved by the Indiana University Institutional Review Board and follows recommendations for intervention trials according to the SPIRIT checklist [24]. The Research Collaboration Agreement signed by NH administrators and Indiana University includes data privacy and protection provisions. Study data are entered into a secure REDCap database to which only study personnel have access.

Potentially eligible residents are identified by the NH leadership, with eligibility confirmed by research staff. A study information sheet (see Additional File 1) and consent form, with opt-out instructions (see Additional File 2), are mailed to the surrogate decision-maker for each resident. Surrogate decision-makers can opt the resident out of the study via phone, email, or REDCap link. An opt-out consent process for residents has been determined to be appropriate for this minimal-risk study. Consent for treatment must be obtained separately prior to a PC clinical consult taking place.

For outcome assessments, staff members who are familiar with the health and care of the enrolled residents over the past 30 days are identified by supervisors or by asking staff directly which residents they know best. Research staff, presenting the study information sheet (see Additional File 3) then approach staff to enroll them in the study and collect outcome data. A staff member may provide outcome data for more than one resident. Documented verbal consent by the staff member is obtained at the time of enrollment. In addition, research staff enroll surrogate decision-makers, typically family members, for outcome assessments. Surrogate contact information is obtained from the NH. Verbal consent is obtained and documented prior to surrogate participation in outcome assessments.

Frontline clinical staff (e.g., nurses and nursing assistants) are offered the Palliative Care Survey [25–27], which includes a study information sheet that states that completion of the survey indicates consent for data to be analyzed.

### Description of the intervention

#### PC Lead role

In-house PC Leads (minimum of 2 per facility, at least one RN or LPN) are existing NH staff members identified to champion NH-based delivery of the intervention. The research team encourages interdisciplinary representation among the PC leads, which may include nurses, social services providers, or chaplains, based on the roles and existing skill sets within the facility. The involvement of nursing is considered key for symptom assessment and management. The UPLIFT-AD research team developed a specialized training framework for leads, which includes approximately eight hours of training content delivered by an experienced PC clinician educator that covers four core modules: An overview of PC in the NH; team and family communication, including content on dementia-specific advance care planning approaches; pain and symptom management; and emotional support and self-care (see Table 1). Leads are also trained to conduct PC assessments, implement strategies to address common symptom/psychosocial/spiritual needs, support residents’ families, facilitate case reviews, and make referrals to the PC consultants. Lead education is designed to be delivered either in-person or virtual, depending on facility and staff preferences.

**Table 1 Tab1:** Palliative care lead education topics

• Overview of UPLIFT
• Resident-Centered Dementia Care
• Palliative and End-of-Life Care
• Communication Part 1: Fundamentals
• Communication Part 2: Advance Care Planning
• Promoting Resident Quality of Life
• Common Distressing Symptoms Part 1: Pain
• Common Distressing Symptoms Part 2: Other Symptoms
• Palliative Care Assessment and Screening
• Taking Care of Yourself
• Ethical, Legal, Financial, and Cultural Considerations

#### All staff education

Providing education on PC to all staff interacting with UPLIFT-AD residents in the facility is a core element of the UPLIFT-AD intervention. Experienced clinical educators from the research team and the external specialty PC consultants—all with extensive expertise in geriatrics and PC—collaborate on delivering education. Key topics include an overview of PC, objectives of the UPLIFT-AD project, resident-centered dementia care, and communication with families. These sessions are delivered as part of all-staff meetings, as well as smaller group sessions which may be held in “huddles” in clinical areas. Additional topics are added upon request from staff, for example, managing difficult dementia-related behavior.

#### PC screening

A key challenge for PC specialty providers is identifying residents appropriate for clinical consults. All participating facilities are implementing a structured process for resident PC needs assessment. PC Leads complete these assessments and determine whether there is a clinical need for PC consultation. The screening tool (see Additional File 4) was developed by the research team, with input from clinical PC partners. It includes absence of, or conflict around, goals of care documentation; poorly managed symptoms; recent hospitalization; polypharmacy; significant functional decline; or other PC needs identified by a PC Lead or other clinical provider.

### Palliative care consultations

PC consultants from a hospital-based PC practice (Indiana) and a large community-based hospice and PC organization (Maryland) are providing on-site consultation visits with residents during the implementation period. Project funds are dedicated to the PC consultant team for a registered nurse’s (RN) or nurse practitioner’s (NP) time to support the capacity building needed to coordinate and deliver specialty care to residents. Consultants (MDs and NPs) can also bill Medicare Part B for billable clinical encounters.

Using the PC screening tool, PC Leads support PC consultants in identifying residents for clinical consults. PC consultants have a consistent schedule in the facility (e.g., ½ day per week or a full day twice monthly). When hospice services are initiated for a resident in the intervention, the in-house PC Leads continue to provide supportive services to the resident and family; however, the PC consultant team transfers clinical care to the hospice providers.

### Flexible and core elements

Nursing homes are dynamic clinical environments and often experience challenges in recruiting and maintaining a well-prepared workforce. As a result, staff often have multiple roles, such as supporting new admissions, scheduled tasks and assessments, routine care, and responding to acute changes in status. Staff and administrator turnover is also common [28]. The research team has extensive experience working in and implementing programs in this setting and familiarity with the reality of complex clinical workflows and stressors. The UPLIFT-AD intervention was designed to optimize implementation through incorporating core elements, as well as built-in flexibility for other elements (see Table 2).

**Table 2 Tab2:** UPLIFT intervention elements

**Core Intervention Elements**	**Flexible Intervention Elements**
• External PC consultations on-site	• Visit schedule
• In-house PC Leads	• Job role of the leads – RN, LPN, social services, or chaplain
• NH staff participation in education	• Schedule of education topics and format of delivery
• Process for PC assessments	• Meeting schedules

### Implementation strategies

The UPLIFT-AD trial includes multiple structured implementation processes. After agreements are signed by corporate and facility level leadership, the kick-off meeting is scheduled. This meeting is attended by NH administrative and clinical leadership, social services, and, when possible, medical providers. The overall rationale and goals of the project are shared, as well as a description of the PC Lead role (see Additional File 5), education topics, PC screening process, and role of PC specialty consultants. A timeline, including detailed description of subject enrollment and data collection, is shared.

Ongoing check-in meetings with research staff and PC Leads throughout the implementation phase allow for monitoring of fidelity to the intervention. These meetings are initially held weekly and then may shift to monthly based on the PC Lead preference after the first month if there is consistent engagement and responsiveness to the research team. During these check-ins, the eligible resident list is reviewed for changes, PC screening status is reviewed, and any troubleshooting regarding PC consults or other issues is discussed.

Any concerns with engagement are generally resolved through communication with the PC Leads or facility-level leadership. The research team also identifies corporate-level contacts for cases when additional support is needed, e.g., IT support to navigate receiving secure emails at the facility for project communications.

Another critical aspect of implementation that requires initial and ongoing management is the communication of recommendations resulting from PC specialty consultations. Recommendations from consultants must be communicated to primary care providers in the facility. Thus, preferences for communication (e.g., use of a folder at the facility; emailing clinical notes) are established upfront and reviewed regularly. A key aspect of the PC Lead role is following up on recommendations from the clinical PC consultants.

### Screening and enrollment

Potentially eligible NH residents are identified and screened by study staff by reviewing a list of potentially eligible residents identified by NH representatives. After NH representatives run a report of the BIMS (Brief Inventory of Mental Status) scores of all residents, the research team reviews eligibility criteria (detailed in the subsequent section) with NH staff for all residents with a BIMS score of 12 or less. All eligible residents’ surrogate decision-makers receive an opt-out letter for resident participation in the study. In accordance with the IRB-approved protocol, if no opt-out response is received within one week of mailing, the residents are then enrolled in the study. The research team collects data from NH staff on all UPLIFT-enrolled residents for the primary study outcomes. Surrogate decision-makers are contacted by phone to enroll them in the study for the purposes of data collection. See Fig. 2 for recruitment data regarding the first 8 facilities through 7/25/22.

**Fig. 2 Fig2:**
[figure not shown]
Overall Patient Study Status for First 8 Facilities (Target *N* = 320), Recruitment start date: 9/1/21. Data current through 7/25/2022

### Inclusion/exclusion criteria

There are three types of research participants in this study: 1) NH residents with indications of cognitive impairment; 2) staff who care for enrolled residents; and 3) surrogate decision-makers (usually family members) of enrolled residents. Inclusion criteria for NH residents are 1) in the facility > 30 days; 2) not currently on Medicare Part A funded rehabilitation care; 3) not receiving hospice services at time of enrollment; and 4) moderate-to-advanced cognitive impairment, with a BIMS score of 12 or less on the most recent assessment prior to enrollment. Inclusion criteria for staff are 1) identified by a supervisor as a person who regularly cares for the resident; 2) employee of the facility; and 3) English-speaking. Inclusion criteria for surrogate decision-makers or family members of residents are 1) familiarity with the care of the resident; and 2) English-speaking. Only one staff member and one surrogate decision-maker provide data for any given resident at each time period; different staff or family members may be enrolled and provide data at later time points for a given resident if needed.

NH staff are recruited to complete Palliative Care Surveys at baseline and six months after implementation. All nursing assistants and licensed nurses (i.e., RNs and LPNs) who interact with UPLIFT-AD residents in the facility are eligible to complete the Palliative Care Survey.

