### Statistical analyses

The primary outcome of the trial is the EOLD-CAD as assessed by NH staff. Family-reported symptom data will be analyzed separately and compared to staff measures for agreement. Analysis will be carried out in an intention-to-treat framework [37]. Consistent with the analysis of stepped wedge trials, we will implement the analysis in mixed-effect models [38]. A key independent variable to be included is the binary indicator for treatment periods (0 = pre-intervention, 1 = post-intervention). Other resident characteristics, such as age, sex, race, and degree of cognitive and functional impairment, will be modeled as covariates. As in trials with a stepped wedge design, all time-invariant resident and facility characteristics will be balanced between the control and intervention periods. Time-varying resident characteristics, however, may be unbalanced. The influences of these factors will be controlled for in the mixed-effects model analysis. Facility-specific random intercepts will be included to accommodate the potential correlations in the outcomes contributed by residents from the same facility. All analyses will be conducted in SAS. The main hypotheses will be tested through PROC MIXED, using a two-sided Wald test. *P* values < 0.05 will be considered statistically significant.

Using the Palliative Care Survey, linear mixed-effects models will be used to compare NH staff PC knowledge and attitudes over time and between conditions. Scores from respondents in the same NH are expected to be correlated; thus, facilities will be included in the model as a random effect. Factors in each model will include respondent and facility characteristics.

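### The staff-rater criteria let PC Leads, who deliver the program, rate the primary outcome; bar them where possible, flag their ratings, and correct the reporter named in Objective 1

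*Protocol article*

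**What the plan says.** **Who rates.** Under Statistical analyses: "The primary outcome of the trial is the EOLD-CAD as assessed by NH staff". Under Inclusion/exclusion criteria: "Inclusion criteria for staff are 1) identified by a supervisor as a person who regularly cares for the resident; 2) employee of the facility"; the third criterion is English-speaking. Research ethics adds that raters should know the resident's care over the past 30 days and that they "are identified by supervisors or by asking staff directly which residents they know best". One staff member may rate several residents, and the rater for a resident may change between rounds.

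**Who the Leads are.** Under PC Lead role, Leads "are existing NH staff members identified to champion NH-based delivery of the intervention". Each facility has at least two, of whom at least one is an RN or LPN. They receive about eight hours of training, which covers pain and symptom management. Under PC screening, they complete the needs assessments, and poorly managed symptoms are one of the items.

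**Which reporter is primary.** Screening and enrollment agrees with Statistical analyses: "The research team collects data from NH staff on all UPLIFT-enrolled residents for the primary study outcomes". Family data have their own role: "Family-reported symptom data will be analyzed separately and compared to staff measures for agreement". Objective 1, however, speaks of "comparing surrogate-reported symptom management and quality of care of residents with dementia in intervention and control periods", while Inclusion/exclusion criteria lists the participant groups separately: "2) staff who care for enrolled residents; and 3) surrogate decision-makers (usually family members) of enrolled residents".

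**The concern.** A Lead meets every stated rater criterion if a supervisor names that Lead as a regular carer. Several features of the plan make this plausible. At least one Lead per facility is a nurse, Leads screen enrolled residents, raters can be found by asking staff whom they know best, and one person may rate many residents.

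A Lead who rates is judging a program that he or she delivers, after training on the symptoms that the scale covers. The analysis rests on a binary pre/post indicator. If Leads rate differently once the program runs, that shift enters the intervention coefficient and the model cannot separate it from a real change in comfort. The shift could go either way: a champion may see improvement, or a trained observer may notice more symptoms and hide a real benefit.

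Objective 1 is a separate and smaller matter. It names a reporter that elsewhere in the article means the family decision-maker, whereas the primary outcome is rated by staff.

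**Working it through.** **1. The plan's own power figure.** Inputs from Power calculation and sample size and from Study design: 16 facilities in four waves of four, 640 residents, effect 0.5 SD, ICC 0.1–0.2, SD about 6 points, two-sided 5% test. The number of ratings per facility-period is not stated, so I varied it. The method is the standard stepped-wedge variance with fixed period effects and a facility random intercept; power = Φ(0.5/SE − 1.96).

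| Assumed layout | ICC | SE (SD units) | Power |
|---|---|---|---|
| 5 periods, 40 per facility-period | 0.1 | 0.0604 | >99.9% |
| T1–T4 schedule, 6-month steps, 40 per facility-period | 0.1 | 0.0723 | >99.9% |
| T1–T4 schedule, 6-month steps, 40 per facility-period | 0.2 | 0.0698 | >99.9% |
| 5 periods, 8 per facility-period (640 ratings in all) | 0.1 | 0.1292 | 97.2% |
| As above, cluster autocorrelation 0.8 | 0.2 | 0.1457 | 93.0% |

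The stated power above 90% is reproduced. It neither supports nor weakens this point, but it gives a range of SEs. I use 0.06–0.13.

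**2. Size of a possible bias.** If Leads give a share *s* of intervention-period ratings and those ratings shift by *d* SD, the coefficient moves by *s × d*. This assumes a constant share and shift after the start and none at T1. Neither *s* nor *d* is in the documents; the values below are assumptions.

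- *s* = 10%, *d* = 0.25: 0.10 × 0.25 = 0.025 SD; × 6 = 0.15 points
- *s* = 10%, *d* = 0.5: 0.10 × 0.5 = 0.05 SD; × 6 = 0.3 points
- *s* = 25%, *d* = 0.5: 0.25 × 0.5 = 0.125 SD; × 6 = 0.75 points

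**3. Effect on the test when there is no true effect.** Rejection probability = Φ(b/SE − 1.96) + Φ(−b/SE − 1.96).

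| Bias b (SD) | SE 0.0604 | SE 0.1292 |
|---|---|---|
| 0.025 | 7.0% | 5.4% |
| 0.05 | b/SE = 0.828: 12.9% + 0.3% = 13.2% | b/SE = 0.387: 5.8% + 0.9% = 6.7% |
| 0.125 | b/SE = 2.070: 54.4% + 0.0% = 54.4% | b/SE = 0.967: 16.0% + 0.2% = 16.2% |

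At the largest SE in the first table, 0.1457, the lower two entries become 6.4% and 13.8%.

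**4. The reporter.** Statistical analyses and Screening and enrollment both name staff. Statistical analyses gives family data a separate role. Only Objective 1 differs.

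**The case against.** The best reply is that this is silence in a condensed article. A full IRB-approved protocol exists, and it may say who cannot rate. Nothing states that Leads do rate. A facility may have only two Leads for about 40 residents, and some may be social services staff or chaplains who would not be named as regular carers. This limits what can be said about frequency. It does not remove the point, because the article does state the rater criteria, and as stated they admit Leads.

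Lead training and baseline collection also fall in the same pre-implementation period, so some Leads may already be trained at T1, which would shrink the before-after shift. That stands, and it makes both size and direction uncertain.

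Barring Leads is only a partial remedy. All staff who interact with enrolled residents receive the education, and no rater is described as blinded. Family members are not free of influence either, since Leads are trained to support them. This also stands. Leads are still the most trained and most invested raters.

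Two stronger readings are tempting. A reader might infer from Objective 1 that the primary source is open to choice between staff and family. It is not: two sections fix staff. Objective 1 also covers quality of care, which EOLD-SWC measures by family report only, so its wording is right for that half. A reader might also infer a false-positive rate of 19–78%. That needs an SE of √(1/640 + 1/1920) = 0.046, meaning all 640 residents rated at all four rounds with no loss and no period term. This is too optimistic a precision for this population.

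**Conclusion.** The point holds as a correctable weakness. The stated rater criteria allow people who deliver the intervention to rate the only primary outcome, in a trial whose rollout order is largely non-randomized.

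The size is unknown. Under the illustrative 10–25% share and 0.5 SD shift, the bias is 0.05–0.125 SD, or 0.3–0.75 points against the 3-point target. The false-positive rate is then about 7–13% at the lower bias and 16–54% at the higher. With a 10% share and a 0.25 SD shift it stays at 5.4–7.0%, close to nominal. Note that 0.5 SD equals the trial's whole target effect, so it is a large assumed shift. These figures show that the matter deserves a safeguard; they do not show that the result will be biased.

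The reporter in Objective 1 is a wording conflict only. The primary source is already fixed as staff.

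**What to change.** 1. Add a staff-rater criterion: not a current or designated PC Lead. Apply it to all remaining rounds, T1 included, where another informed staff member is available. In the same edit, make Inclusion/exclusion criteria and Research ethics agree on how raters are identified, since one names supervisors only and the other also allows asking staff.
2. Record Lead status for every rating, including those already collected. This replaces the assumed share with the observed one.
3. Run the primary model without Lead ratings as a sensitivity analysis.
4. Fit the same model to family-reported EOLD-CAD and name it as the supportive analysis. Family data are already to be analyzed separately, so this mainly fixes the model and its role.
5. Reword Objective 1, for example to staff-reported EOLD-CAD (primary) and family-reported outcomes (secondary).

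The cost is one eligibility line, one objective line, one data field and two model runs. The downside is that a few residents will be rated by the next-best-informed staff member. Rater bias from educated, unblinded staff remains and should be acknowledged when the results are reported.
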